## Abstract

**Background:**

Binge Eating Disorder (BED) represents a common eating disorder associated with marked health impairments. A subclinical variant, loss of control eating (LOC) is prevalent in youth. LOC is associated with similar mental distress as full-blown BED, increases the risk to develop a BED and promotes continuous weight gain. The etiology of LOC is not yet fully understood and specialized treatment for youth is scarce.

**Methods:**

The i-BEAT study includes a cross-sectional and longitudinal online questionnaire study (N = 600), an App based daily-life approach and a laboratory virtual reality study in N = 60 youths (14–24 years) with and without LOC as well as a controlled randomized online treatment trial to investigate the feasibility, acceptance and efficacy of a CBT and an interpersonal emotion regulation module for youth (N = 120). The primary outcomes include self-reported as well as measured (heart rate variability, gaze behavior, reaction times in stop signal task) associations between emotion regulation problems (such as dealing with RS), psychological impairment and binge eating in a healthy control group and youth with LOC. Secondary outcomes encompass general eating disorder pathology, social anxiety, body mass index, hyperscanning behavior and therapists’ rating of patients’ condition pre and post treatment. Epigenetic correlates of RS are assessed in healthy controls and youth with LOC and explored before and after treatment.

**Discussion:**

The expected findings will specify the role of interpersonal emotion regulation problems such as coping with the experience of social exclusion and rejection sensitivity (RS) in LOC and clarify, whether including a training to cope with RS adds to the efficacy of a cognitive behavioral treatment (CBT).

*Trial registration*: German Clinical Trial Register: DRKS00023706. Registered 27 November 2020, https://www.drks.de/drks_web/navigate.do?navigationId=trial.HTML&TRIAL_ID=DRKS00023706

**Supplementary Information:**

The online version contains supplementary material available at 10.1186/s40359-021-00690-8.

## Background

### Binge eating disorder (BED) and loss of control over eating (LOC)

Since the introduction of the fifth version of the Diagnostic and Statistical Manual of Mental Disorders (DSM-5 [1]) in 2013, BED, characterized by recurrent binge eating episodes associated with marked distress represents a separate entity in the section of feeding and eating disorders. BED is relatively common, associated with weight gain and detrimental consequences for mental and physical health [2]. Current research [3, 4] shows that BED variants are common during puberty and early adulthood, a period characterized by rapid biological changes, e.g. growth spurts, brain and secondary sex characteristics development, shifts in the accumulation of body fat. Puberty and early adulthood are furthermore accompanied by psychological challenges such as striving for autonomy and identity based on the acceptance of appearance and interpersonal competences [5]. This period at the age of c. 14 to 24 years has been named *youth* by the UN (www.unesco.org) and is critical for the onset of eating disorders (ED) [6]. A substantial group of youth experiences LOC, defined as loss of control eating over smaller food amounts which do not fulfil the criteria of an objective large food amount as required according to DSM-5, but with equivalent psychopathological relevance [7, 8]. The consequences of LOC in youth include weight gain, stress symptoms, substance use and low quality of life as well as increased suicide risks in female and male youth [9]. There is a consensus to apply age adapted criteria to capture the presentation of youthful BED variants and LOC (the two of them thereafter summarized as LOC). Existing research applies various frequency and duration criteria, from at least one LOC episode during the prior month to once a week during the previous 3 months [4, 10]. Up to now, most of the research in LOC relies on female participants, even though males are more often affected with BED and LOC than in other EDs [11].

### Epidemiology of LOC

Data on prevalence and the course of LOC in youth is scarce. According to a recent review [3] prevalence rates vary from 1 to 5% for BED and from 2.5 to 4.6% for subclinical forms of BED like LOC [12], with higher prevalence of LOC and BED in obese youth than in the general population. One of the rare longitudinal studies on the persistence of LOC in an US cohort found that LOC was significantly related to the stability of ED symptoms over the course of 10 years [13]. Another, smaller study found moderate stability of LOC over a 5-years period [14].

### Interpersonal emotion regulation as a risk factor for LOC

Recent studies on psychological risk factors for the development of disordered eating confirm *dual-pathway models*, where sociocultural influences such as an unrealistic thin ideal are assumed to lead to body dissatisfaction, which promotes dieting and binge eating (e.g. [15]). While data on the dieting pathway remains controversial, the negative affect pathway has been confirmed in cross-sectional and longitudinal studies [16–18]. Recently, the model has been applied to LOC, where dysfunctional short-term emotion regulation strategies to alleviate negative affect play an important role [18]. An impaired awareness, understanding and acceptance of emotions or few appropriate emotion regulation strategies [19] are related to interpersonal problems [20, 21]. It can be assumed that interpersonal problems in youth interact with negative affect and lead to vicious circles promoting continued LOC [22]. Research in youth with LOC has only begun to assess the role of negative interpersonal and appearance-related evaluation, which are likely to be salient at that age [23], and therefore the sensitivity to general or appearance-related rejection (referred to as rejection sensitivity, RS) also gained interest [24]. RS describes an individual’s tendency to anxiously expect, readily perceive and overact to real or imagined rejection; often associated with past and current adverse experiences [25]. In youth, questionnaire-assessed appearance-related RS independent of gender, was related to dysfunctional eating behavior, lower self-esteem and more frequent experience of appearance-related teasing [26]. So far, there is only one laboratory study in youth with LOC which underlines the effect of negative peer evaluation in a small sample of overweight to obese females. In this study, the fictitious evaluation by peers based on photographs of the participants was associated with increased activation of anxiety related brain regions and failure to engage prefrontal cortex regions involved in emotion regulation attempts, all of which might be alleviated by overeating [27]. An increased RS in interaction with impaired emotion regulation and negative affect or mood has the potential to promote the development and maintenance of LOC in youth, but needs further clarification (Fig. 1). In addition, it can be assumed that the continued experience of rejection threatens the homeostasis of a person’s milieu, leads to a prolonged physiological stress response and might contribute to the intake of palatable food at an increased eating rate [28] and therefore to overeating and LOC. The capacity of the organism to adequately respond to stress conditions depends on the flexibility of the autonomic nervous system (ANS) which is connected to the amygdala and the medial prefrontal cortex and is indexed by heart rate variability (HRV) [29]. Reduced emotion regulation abilities are common in adults with EDs, but little is known about similar difficulties in youth with LOC [30, 31]. Consequently, investigating HRV responses to being exposed to social exclusion might help to understand emotion regulation skills in stressful situations and clarify the impact on LOC.

**Fig. 1 Fig1:**
[figure not shown]
Working model of the role of interpersonal emotion regulation problems, rejection sensitivity, in youth with LOC

### Treatment research in LOC

Despite the relatively high prevalence of LOC in youth and the negative effects on mental and physical health, studies on psychological treatments in youth are scarce [32]. The existing evidence from diverse samples regarding LOC in youth point to the efficacy of cognitive behavioral therapy (CBT) [33], interpersonal therapy (IPT) [34] or dialectic behavioral therapy (DBT) [35] in reducing binge eating frequency. One online treatment study applied CBT to a sample of 105 male and female high school students at risk for overweight and/ or with overeating or LOC at a mean age of 15 years. The online treatment resulted in decreased LOC episodes and a moderate weight reduction up to the 9 months follow-up [36]. Consequently, it can be assumed, that an explicit focus on eating behavior as in CBT for eating disorders (CBT-E) might be appropriate for youth [33], but there is further promise in targeting interpersonal emotion regulation deficits, leading to negative affect and LOC [34], while the differential or additive efficacy of CBT-E and interventions on interpersonal emotion regulation in female and male youth needs further investigation.

## Methods/design

### Study aims and hypotheses

The general aim of the i-BEAT (online Binge Eating for Adolescent Treatment) study is to explore the role of interpersonal emotion regulation in terms of social exclusion and RS in youth with LOC compared to a healthy control group (HCG). The investigation includes a cross-sectional and longitudinal questionnaire and an App based daily-life self-report assessment about the association of negative affect, social rejection, RS, emotion regulation difficulties and LOC episodes (study 1), a laboratory based virtual reality (VR) cyber ball task to address the effects of social exclusion on psychological and physiological correlates of stress and a gamified Stop Signal Task (gSST) to assess behavioral motor inhibition capacities (study 2) and a randomized controlled online treatment trial to investigate the separate (superiority for specific outcomes) and additive effect of a self-help CBT-E and an interpersonal emotion regulation module for eating disorders (INTER-E) (study 3).

The following hypotheses are addressed in the three substudies:

Hypotheses concerning (1) primary and (2) secondary outcomes in study 1:Questionnaire and App based daily-life assessed RS at baseline is positively associated with the number of weekly LOC episodes, ED pathology, past and current exclusion experiences, emotion regulation difficulties, impaired mental health and with Body Mass Index (BMI) in all groups. Questionnaire and App based daily-life assessed RS at baseline is positively associated with the number of weekly LOC episodes, ED pathology, past and current exclusion experiences, emotion regulation difficulties, impaired mental health and with Body Mass Index (BMI) in all groups.Rejection sensitivity at baseline is positively associated with the number and severity of LOC episodes, with problems of emotion regulation, impaired mental health and with ED pathology at year 2.Emotional eating and/or LOC episodes in daily-life result in a short-term reduction of negative affect but contribute to increased body dissatisfaction, especially in youth with LOC.Lower inhibition capacities precede and predict weekly LOC episodes, emotional eating and urge to eat.Lower inhibition capacities correlate with impaired mental health.Effects become stronger with increasing values of RS.

Hypotheses concerning (1) primary and (2) secondary outcomes in study 2:Exposure to the exclusion condition of the VR Cyberball task leads to greater social threat-related effects during and after the exclusion (lower HRV; increased negative/reduced positive affect, impairment of basic needs) and to a delayed recovery in youth with LOC compared to the HCG. Exposure to the exclusion condition of the VR Cyberball task leads to greater social threat-related effects during and after the exclusion (lower HRV; increased negative/reduced positive affect, impairment of basic needs) and to a delayed recovery in youth with LOC compared to the HCG.Exposure to the exclusion condition leads to higher values of body dissatisfaction and of urge to engage in disinhibited eating after the task and during recovery in youth with LOC compared to HCG.RS interpretation bias (underestimation of ball tosses while included, misinterpretation as being excluded during inclusion condition, negative evaluation of ambiguous social scenarios) is more pronounced in youth with LOC than in the HCG.Exposure to the exclusion condition leads to stronger pupillary dilation response, stronger hyperscanning (eye gaze), more closed hand posture, stronger aversion of social gaze (measured as gaze dwell time) in youth with LOC compared to the HCG.Youth with LOC show lower motor inhibition capacities indicated by longer SSRTs than the HCG during the gSST.The motor inhibition capacity group difference is especially apparent in the food stimuli condition of the gSST in the LOC group compared to the HCG.

Hypotheses concerning (1) primary and (2) secondary outcomes in study 3:Applying an INTER-E or a CBT-E module leads to a greater reduction of the number and severity of LOC episodes, problems of emotion regulation and negative mood than a 4-weeks’ waiting period.The INTER-E module reduces weekly RS experiences, negative mood and problems of emotion regulation more strongly than the CBT-E module, whereas CBT-E decreases numbers and severity of weekly LOC episodes and urge to engage in disinhibited eating more importantly than the INTER-E module.Applying the additional CBT-E or INTER-E module results in additional improvement of RS experiences, numbers or severity of weekly LOC episodes, problems of emotion regulation and urge to engage in disinhibited eating.BMI remains stable during active treatment and follow-up.Effects of the initial INTER-E or the CBT-E module remain stable during a 3-weeks pause.Effects of the treatment remain stable during 6- and 12-months follow-up.Therapist ratings of improvement are in line with the self-report of the patients.CBT-E and INTER-E result in similar acceptance, usability, attrition and adherence rates.

We further aim to explore epigenetic underpinnings (DNA methylation, DNAm) of RS and emotion regulation capacity [37]. DNAm patterns are thought to reflect exposure to various psychosocial influences across the life-span and have been shown to relate to behavioral, emotional and cognitive styles especially in youth [38, 39]. We seek to explore the DNAm levels of genes involved in stress regulation and social interaction (FK-506-binding protein 5 (FKBP5) [40], the glucocorticoid receptor (NR3C1) [41], oxytocin receptor (OXTR) [42, 43] and the serotonin transporter (SLC6A4) in youth with LOC compared to a HCG (prior to treatment) and in LOC prior versus post treatment.

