### Sample size

For study 1 we will recruit N = 600 youth and expect a participation rate of c. 70–80% after one year. Power is sufficient (1−β = 0.8) to detect small to medium effect sizes *f*^2^ of c. 0.08, applying multiple regression models including covariates and testing specific predictors, for a given β of 0.05. For the App based study 1 multilevel models are applied to carry out between-subjects analysis of covariance. Moderators will be included to test for the interaction effects between groups (LOC vs HCG) within the Cyberball task. We expect moderate to large effect sizes (d = 0.8) with sufficient power to detect significant effects given 1−b = 0.8 and a = 0.05 for study 2 with N = 60 youths, even when accounting for c. 13% dropouts. For study 3, mixed between and within-subjects analysis of covariance or linear mixed models are carried out. Based on our BEAT pilot trial (DRKS00014580), where a high effect size for within subject measures revealed (d = 1.37) a medium to high effect size for these effects can be assumed (f = 0.25, taking r = 0.5 for the correlation among repeated measures), the required sample size would be N = 34 with sufficient power to detect significant effects given 1−β = 0.8 and β = 0.05 for study 3 with N = 120 youths, even when accounting for dropouts. Exploratory epigenetic goals involve predictors and within-subject effects and are expected to be sufficiently powered if effect sizes are medium to large (Fig. 3 depicts the study sample).

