### Data analysis

Data will be analyzed with the Statistical Package of Social Sciences (SPSS) and R. We will apply multiple regression models including covariates and testing specific predictors (study 1), multilevel models including moderators (App based study 1), between subjects analysis of covariance including moderators (study 2) and mixed between and within subjects analysis of covariance or linear mixed models (study 3). Exploratory epigenetic goals involve predictors and within-subject effects. Expected dropouts are assumed to amount up to 10–18%. Random occurrence should lead to equal distribution of dropouts in the different groups (LOC vs. HCG; CBT-E first vs. INTER-E first). However, in the case of an unequal distribution of the number of participants to the different groups, this issue will be addressed with multi-level models. Multi-level models are assumed to be robust against violations of equal group sizes [55]. Additionally, we will test whether a missing at random pattern is a reasonable assumption with respect to dropout.

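### Study 3 states hypotheses of stability and similarity without any bound, while its stated analysis and power address only the detection of differences

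*Protocol article*

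**What the plan says.** The study 3 list in *Study aims and hypotheses* contains four statements of no change or no difference:

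- "BMI remains stable during active treatment and follow-up"
- "Effects of the initial INTER-E or the CBT-E module remain stable during a 3-weeks pause"
- "Effects of the treatment remain stable during 6- and 12-months follow-up"
- "CBT-E and INTER-E result in similar acceptance, usability, attrition and adherence rates"

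None carries a bound. The same section gives the aim of the trial as "to investigate the separate (superiority for specific outcomes) and additive effect of a self-help CBT-E" and of an interpersonal module. *Study design* says that changes between successive time points, including the pause and the follow-ups, are compared. *Data analysis* names "mixed between and within subjects analysis of covariance or linear mixed models (study 3") and nothing else for this study. *Sample size* assumes f = 0.25, "taking r = 0.5 for the correlation among repeated measures", states that "the required sample size would be N = 34", and plans 120 participants with power 0.8 to find significant effects. *Data analysis* expects 10–18% dropout and assumes that it will fall equally on the two module orders.

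**The concern.** A hypothesis of stability or similarity is supported when the data exclude a change or gap large enough to matter. Without a stated bound it can be neither confirmed nor refuted. If such a hypothesis is judged by whether a difference test is significant, it becomes easier to confirm as data are lost, which is the wrong direction.

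At stake are a claim that benefit is maintained when there has been relapse, and a claim that the modules are equally acceptable when one loses more participants. The abstract names feasibility and acceptance as trial aims beside efficacy, so these are not side questions. The assumption of equal dropout across module orders also presupposes part of what the similarity hypothesis is meant to examine.

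BMI has a further difficulty. Eligibility runs from 14 to 24 years, and the *Background* itself describes growth spurts and shifts in body fat in this period. In minors, raw BMI over more than a year mixes growth with any treatment effect.

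**Working it through.** **Inputs from the protocol article.** N = 120, f = 0.25, r = 0.5, power 0.8, dropout 10–18% (108 to 98 completers). **Assumptions.** Two-sided alpha 0.05 (the text prints a second β at that place); 1:1 allocation, hence 60 per arm (permuted blocks are stated, the ratio is not); all bounds below.

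**1. The plan's own figure.** Repeated-measures ANOVA with two measurements: λ = f²·N·m/(1−r) = 0.0625 × 34 × 2/0.5 = 8.5. With two groups this gives power 0.807 at N = 34, so the stated figure is reproduced. It is a calculation for detecting a difference. With 98 to 120 participants, power for that effect exceeds 0.99, but this says nothing about showing similarity.

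**2. Attrition between arms.** The 95% half-width is 1.96·√(2p(1−p)/60).

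- p = 0.10: 1.96 × 0.0548 = 10.7 points
- p = 0.18: 1.96 × 0.0701 = 13.7 points

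Power of a difference test, normal approximation with pooled variance under the null:

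| True rates | Power | Non-significant |
|---|---|---|
| 10% v 18% | 0.24 | 76% |
| 13% v 23% | 0.30 | 70% |

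The first row uses the two ends of the plan's dropout range as illustrative arm rates.

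**3. Acceptance or usability scores between arms.** With 49 to 60 per arm, a true gap of 0.3 SD is missed 68% to 62% of the time.

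**4. Within-person stability.** In SD units, SE = √(2−2r)/√n = 1/√98 = 0.101.

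- Difference test, true change 0.2 SD: Φ(1.98 − 1.96) = 0.51, so missed 49% of the time.
- Difference test, true change 0.3 SD: Φ(2.97 − 1.96) = 0.84.
- One-sided non-inferiority, bound 0.3 SD worsening, one-sided 5% level, true change zero: Φ(2.97 − 1.645) = 0.91. The same formula gives 0.81 at r = 0.3 and 0.99 at r = 0.7.
- A two-sided ±0.3 SD bound would penalise continued improvement. With a true further gain of 0.2 SD it would conclude *stable* only Φ(0.99 − 1.645) = 26% of the time. The one-sided bound would be met more than 99% of the time.

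**5. What bound is usable for attrition?** A ±20-point bound exceeds the whole expected dropout. Judged by a 90% interval, it would call 13% v 23% similar with probability Φ(0.10/0.0701 − 1.645) = 0.41. With a 95% interval, a 10-point bound is out of reach at 10–18% dropout, because the half-width already exceeds 10 points. For 80% power it would need 190, 254 or 311 per arm at 10%, 14% or 18% dropout. A 15-point bound at 18% dropout would be met 14% of the time under equal true rates.

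**6. BMI.** Suppose growth adds 0.3–0.5 kg/m² in participants under 18 and the SD of change is 1.5 (both assumed), so SE = 1.5/√98 = 0.152. If minors are 4/11 of the sample (four of the eleven eligible years of age), the mean shift is 0.11–0.18, and a difference test declares change from growth alone 11–22% of the time. With half the sample under 18 this is 17–38%.

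**The case against.** A reader might infer that these hypotheses will be tested with difference tests and that non-significance will be taken as proof. The article does not say so. It assigns no test to them, ANCOVA and mixed models are not natural methods for attrition rates, and a mixed model yields the confidence intervals that an equivalence judgement needs. This stands, so the point concerns missing bounds and a framework built for differences, not a stated misuse.

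A full protocol or analysis plan, not shown, may define bounds and BMI standardisation. That is fair for the mechanics. But the bound is part of the hypothesis itself, and every analytic element the article does state points to detecting differences.

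The sample is not small for every one of these hypotheses. Three of the four are within-person, and there a 0.3 SD change is already detected with 84% power. Participants are also scheduled for both modules, so acceptance and adherence have within-person data that the two-arm figures ignore. Both points stand and confine the weakness mainly to comparisons between arms, attrition above all.

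On BMI, a reader might infer that growth alone would make a finding of change likely: 51–91% under the same assumed inputs if everyone were growing. That applies adolescent growth to a sample reaching age 24, which the eligibility criteria do not support. The error also runs the other way, towards falsely rejecting stability.

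**Conclusion.** The concern holds in this form: study 3 sets out stability and similarity hypotheses with no bound, and the analysis and power it describes address differences only. A non-significant result could be taken as support while being weak evidence. The weakness is greatest for attrition between arms, where the interval is about ±11 to ±14 points at 10–18% dropout, assuming 60 per arm. It is milder for maintenance of effects: a 0.2 SD relapse would be missed 49% of the time with 98 completers and r = 0.5, but a 0.3 SD bound can be tested well in the planned sample. The size of the BMI bias depends on the share of minors, which is not stated. The rank of these hypotheses as primary or secondary cannot be read from the available text. The bounds used here are illustrations, and the article offers none to compare them with.

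**What to change.** Before analysis, set a bound with a stated justification for each hypothesis and judge it by confidence interval.

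- **Maintenance over the pause and at 6 and 12 months:** a one-sided non-inferiority bound, for example 0.3 SD worsening, with the one-sided level stated.
- **BMI:** a two-sided bound. Analyse participants under 18 on an age- and sex-standardised score.
- **Attrition, adherence, acceptance, usability:** report the difference with its 95% interval. Conclude *similar* only if the interval excludes a pre-stated relevant gap smaller than the expected dropout rate. Otherwise call the result inconclusive, or label the hypothesis descriptive from the start. For attrition the sample will seldom allow more than this.

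The cost is analysis wording, with no extra participants. The downside is that some hypotheses will end as inconclusive where a non-significant test might have been reported as support.
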